| Creatine Kinase                          | 3.0 – 5.9 x ULN †             | 6.0 – 9.9 x ULN †           | 10.0 – 19.9 x ULN †                                        | ≥ 20.0 x ULN †                                                                                            |
| Creatinine                               | 1.1 – 1.3 x ULN †             | 1.4 – 1.8 x ULN †           | 1.9 – 3.4 x ULN †                                          | ≥ 3.5 x ULN †                                                                                             |
| Glucose, serum, high                     |                                          |                                        |                                                                       |                                                                                                                      |
| Nonfasting                               | 116 – 160 mg/dL
6.44 – 8.88 mmol/L    | 161 – 250 mg/dL
8.89 – 13.88 mmol/L | 251 – 500 mg/dL
13.89 – 27.75 mmol/L                               | > 500 mg/dL
> 27.75 mmol/L                                                                                        |
| Fasting                                  | 110 – 125 mg/dL
6.11 – 6.94 mmol/L    | 126 – 250 mg/dL
6.95 – 13.88 mmol/L | 251 – 500 mg/dL
13.89 – 27.75 mmol/L                               | > 500 mg/dL
> 27.75 mmol/L                                                                                        |
| Glucose, serum, low                      |                                          |                                        |                                                                       |                                                                                                                      |
| Adult and Pediatric ≥ 1 month     | 55 – 64 mg/dL
3.05 – 3.55 mmol/L      | 40 – 54 mg/dL
2.22 – 3.06 mmol/L    | 30 – 39 mg/dL
1.67 – 2.23 mmol/L                                   | < 30 mg/dL
< 1.67 mmol/L                                                                                          |
| Infant*†, < 1 month | 50 – 54 mg/dL
2.78 – 3.00 mmol/L      | 40 – 49 mg/dL
2.22 – 2.77 mmol/L    | 30 – 39 mg/dL
1.67 – 2.21 mmol/L                                   | < 30 mg/dL
< 1.67 mmol/L                                                                                          |
| Lactate                                  | < 2.0 x ULN without acidosis             | ≥ 2.0 x ULN without acidosis           | Increased lactate with pH < 7.3 without life-threatening consequences | Increased lactate with pH < 7.3 with life-threatening consequences                                                   |
| LDL cholesterol (fasting)                |                                          |                                        |                                                                       |                                                                                                                      |
| Adult ≥ 18 years                  | 130 – 159 mg/dL
3.37 – 4.12 mmol/L    | 160 – 190 mg/dL
4.13 – 4.90 mmol/L  | ≥ 190 mg/dL
≥ 4.91 mmol/L                                          | NA                                                                                                                   |
| Pediatric > 2 - < 18 years  | 110 – 129 mg/dL
2.85 – 3.34 mmol/L    | 130 – 189 mg/dL
3.35 – 4.90 mmol/L  | ≥ 190 mg/dL
≥ 4.91 mmol/L                                          | NA                                                                                                                   |
| Lipase                                   | 1.1 – 1.5 x ULN                          | 1.6 – 3.0 x ULN                        | 3.1 – 5.0 x ULN                                                       | > 5.0 x ULN                                                                                                          |
| Magnesium, serum, low                    | 1.2 – 1.4 mEq/L
0.60 – 0.70 mmol/L    | 0.9 – 1.1 mEq/L
0.45 – 0.59 mmol/L  | 0.6 – 0.8 mEq/L
0.30 – 0.44 mmol/L                                 | < 0.60 mEq/L
< 0.30 mmol/L                                                                                        |
| Pancreatic amylase                       | 1.1 – 1.5 x ULN                          | 1.6 – 2.0 x ULN                        | 2.1 – 5.0 x ULN                                                       | > 5.0 x ULN                                                                                                          |
| Phosphate, serum, low                    |                                          |                                        |                                                                       |                                                                                                                      |
| Adult and Pediatric > 14 years | 2.5 mg/dL – < LLN
0.81 mmol/L – < LLN | 2.0 – 2.4 mg/dL
0.65 – 0.80 mmol/L  | 1.0 – 1.9 mg/dL
0.32 – 0.64 mmol/L                                 | < 1.00 mg/dL
< 0.32 mmol/L                                                                                        |
| Pediatric 1 year – 14 years       | 3.0 – 3.5 mg/dL
0.97 – 1.13 mmol/L    | 2.5 – 2.9 mg/dL
0.81 – 0.96 mmol/L  | 1.5 – 2.4 mg/dL
0.48 – 0.80 mmol/L                                 | < 1.50 mg/dL
< 0.48 mmol/L                                                                                        |
| Pediatric < 1 year             | 3.5 – 4.5 mg/dL
1.13 – 1.45 mmol/L    | 2.5 – 3.4 mg/dL
0.81 – 1.12 mmol/L  | 1.5 – 2.4 mg/dL
0.48 – 0.80 mmol/L                                 | < 1.50 mg/dL
< 0.48 mmol/L                                                                                        |
| Potassium, serum, high                   | 5.6 – 6.0 mEq/L
5.6 – 6.0 mmol/L      | 6.1 – 6.5 mEq/L
6.1 – 6.5 mmol/L    | 6.6 – 7.0 mEq/L
6.6 – 7.0 mmol/L                                   | > 7.0 mEq/L
> 7.0 mmol/L                                                                                          |

| LABORATORY                                                           |                                                               |                                                               |                                                                 |                                                          |
|----------------------------------------------------------------------|---------------------------------------------------------------|---------------------------------------------------------------|-----------------------------------------------------------------|----------------------------------------------------------|
| PARAMETER                                                            | GRADE 1
MILD                                               | GRADE 2
MODERATE                                           | GRADE 3
SEVERE                                               | GRADE 4
POTENTIALLY
LIFE-THREATENING               |
| Potassium, serum, low                                                | 3.0 – 3.4 mEq/L
3.0 – 3.4 mmol/L                    | 2.5 – 2.9 mEq/L
2.5 – 2.9 mmol/L                    | 2.0 – 2.4 mEq/L
2.0 – 2.4 mmol/L                      | < 2.0 mEq/L
< 2.0 mmol/L                    |
| Sodium, serum, high                                                  | 146 – 150 mEq/L
146 – 150 mmol/L                    | 151 – 154 mEq/L
151 – 154 mmol/L                    | 155 – 159 mEq/L
155 – 159 mmol/L                      | ≥ 160 mEq/L
≥ 160 mmol/L                       |
| Sodium, serum, low                                                   | 130 – 135 mEq/L
130 – 135 mmol/L                    | 125 – 129 mEq/L
125 – 129 mmol/L                    | 121 – 124 mEq/L
121 – 124 mmol/L                      | ≤ 120 mEq/L
≤ 120 mmol/L                       |
| Triglycerides (fasting)                                              | NA                                                            | 500 – 750 mg/dL
5.65 – 8.48 mmol/L                  | 751 – 1,200 mg/dL
8.49 – 13.56 mmol/L                 | > 1,200 mg/dL
> 13.56 mmol/L                |
| Uric acid                                                            | 7.5 – 10.0 mg/dL
0.45 – 0.59 mmol/L                 | 10.1 – 12.0 mg/dL
0.60 – 0.71 mmol/L                | 12.1 – 15.0 mg/dL
0.72 – 0.89 mmol/L                  | > 15.0 mg/dL
> 0.89 mmol/L                  |
| URINALYSIS Standard International Units are listed in italics |                                                               |                                                               |                                                                 |                                                          |
| Hematuria (microscopic)                                              | 6 – 10 RBC/HPF                                                | > 10 RBC/HPF                                                  | Gross, with or without
clots OR with RBC
casts            | Transfusion indicated                                    |
| Proteinuria, random
collection                                    | 1 +                                                           | 2 – 3 +                                                       | 4 +                                                             | NA                                                       |
| Proteinuria, 24 hour collection                                      |                                                               |                                                               |                                                                 |                                                          |
| Adult and Pediatric
≥ 10 years                            | 200 – 999 mg/24 h
0.200 – 0.999 g/d                 | 1,000 – 1,999 mg/24 h
1.000 – 1.999 g/d             | 2,000 – 3,500 mg/24 h
2.000 – 3.500 g/d               | > 3,500 mg/24 h
> 3.500 g/d                 |
| Pediatric > 3 mo -
< 10 years                       | 201 – 499 mg/m  /24 h
0.201 – 0.499 g/d | 500 – 799 mg/m  /24 h
0.500 – 0.799 g/d | 800 – 1,000 mg/m  /24 h
0.800 – 1.000 g/d | > 1,000 mg/m  /24 h
> 1.000 g/d |

## APPENDIX 9: ADDITIONAL BACKGROUND INFORMATION

### (I) The immune response to HIV

#### (i) The role of T-cells

Whilst CD4 T-cells are key regulators of humoral and cellular adaptive immune responses, CD8 T-cells have often been the main focus of T-cell vaccine development because they are able to kill virally infected cells. HIV specific T-cell responses contribute directly towards protective immunity in those that are naturally infected [1][2] and the development of such cellular responses coincides with the control of acute HIV-1 viremia in both humans and macaques. This has been taken as evidence that T-cells are instrumental in controlling viral replication, especially as there is no such correlation between the kinetics of viral control and appearance of Ab responses. Recent work in animal models has suggested that recombinant viral vectors which stimulate a broad and strong CD8+ T-cell response can also partially protect against challenge with the highly virulent SIV mac239 strain [3][4] and a recently described macaque model using a cytomegalovirus vector able to continuously deliver SIV antigens suggests that the persistence of immune response might be central to efficacy. One area which is particularly poorly understood is why so many SIV and HIV-specific T-cells are so poor at killing virally infected (as opposed to peptide pulsed) target cells *in vitro* [5] and a deeper understanding of the relationship between the phenotype of a T-cell and its protective potential is urgently needed. There is also a need for studies employing “functional” readouts which better reflect what is needed to control a natural infection. Ideally these assays should also be validated for incorporation as endpoints in clinical trials [6].

#### (ii) The role of antibodies

Passive transfer experiments in macaques have already shown that broadly physiological levels of an existing broadly neutralising antibody are able to block infection following low dose intra-vaginal challenge with SIV [7, 8] and whilst immunogens are designed, plans are underway to conduct passive transfer studies with human monoclonal neutralising antibodies to see whether this would also be feasible as a prevention strategy. Non-neutralising antibodies have come back into the spotlight again in light of the results of RV144 and there are passive transfer studies underway in NHP using monoclonal antibodies derived from those which were shown to correlate with reduced risk of infection.

It is still far from clear how to induce neutralising antibody responses with a vaccine. A significant minority of HIV infections result in heterogeneous mixtures of polyclonal broadly neutralising antibodies with broad specificity for the virus envelope [9]. After a concerted effort several broadly neutralising antibodies have been isolated from HIV infected individuals and cloned. Whilst these can inform rational design, the affinity maturation of these broadly neutralising antibodies is not well understood and it seems more complex than for other humoral responses. The antibodies elicited by vaccines to date have not been protective and many of the most relevant epitopes on the viral envelope remain undefined. Some of the underlying reasons for this are now being understood. The target of the most potent neutralising antibodies, the envelope spike, is very unstable and difficult to synthesise in the relevant immunogenic form [10] and the most conserved epitopes within this spike are some of the most difficult to access [11]. Even if it were possible to induce neutralising antibodies, access to infectious virions might also prove limiting. Importantly, it is also not yet known whether virus is transmitted in a predominantly cell-free or intracellular form *in vivo* and it is also still far from clear precisely how the virus passes between cells. This is particularly relevant because there is some doubt about any role for neutralising antibodies in processes such as synapse mediated transmission [12]. It is anticipated that the insights gained from

the structural analysis of naturally occurring antibodies will feed directly into rational vaccine design [13].

### **(iii) RV144 and immune correlates protection**

Elispot T-cell responses were only seen in ~17% of vaccinees and there were no T-cell responses which correlated with protection from infection, although >90% of those vaccinated made non-neutralising (and relatively short-lived) antibody responses to the vaccine. The exhaustive immunological analysis of available samples from a small subset of the cohort has very recently been completed and initial results (unpublished) suggest that circulating levels of IgG non-neutralising antibodies with specificity for the V1/V2 loop of the viral envelope are correlated with a reduced risk of subsequent infection whereas levels of IgA of the same specificity are positively correlated with risk of infection [14]. The latest results have had a significant impact on the field, shifting strategic focus back to antibodies and impacting on the design of ongoing trials. Initially, the strategic focus of the field was protective antibodies and when there was no demonstrable efficacy using this approach in clinical trials, the emphasis switched to the development of T-cell immunogens. The first efficacy trials (VAXgen) started in North America and Europe in 1998 and in Thailand in 1999, and assessed the efficacy of a recombinant gp120 HIV-1 envelope protein (AIDSVAX B/E). Preliminary results from the North American Phase III randomised trial which recruited 5095 individuals, showed that whilst the protein used was safe and immunogenic, it failed to confer protection [15]. Results from the trial in Thailand endorsed the findings in a different setting [16]. Two large phase IIB trials of a "T-cell vaccine" (STEP and Phambili) using a non-replicating recombinant Adenovirus 5 vector encoding subtype B gag, pol and nef were terminated due to futility and worryingly, because there was also a suggestion of increased risk of HIV acquisition in some of those who received the vaccine- although whether this increased susceptibility was caused by vaccine itself is still debated [17, 18].


responses were relatively weak and the results have not shifted the consensus view that the optimal vaccine against HIV would need to generate strong cellular and humoral immune responses- both of which have been shown to contribute to control of natural infection.

#### **(iv) Current vaccination strategies**

Host responses to natural and experimental infections suggest that there are protective immune responses which could be harnessed by a vaccine [19, 20]. Interestingly, although associated with a ~31% reduction in infection, vaccination in RV144 was not associated with a reduction in viral load set point or any other sustained clinical parameters related to improved outcomes [20].

Immune correlates of protection are poorly understood but it is now widely agreed that broad and durable humoral and cellular immune responses are both needed - ideally present at the portals of virus entry at the time of first exposure. Nonhuman primate models have been extensively used to assess vaccine efficacy in experimental challenge studies and the limitations and potential relevance of such models to vaccine efficacy have been reviewed elsewhere [21]. More than 30 candidate HIV vaccines have been taken forward into early phase clinical trials on the basis of the demonstration of efficacy in nonhuman primates but to date this has only translated in to one (modestly) successful trial in humans.

#### **(v) Heterologous prime boost vaccination regimes.**

In a trial which enrolled participants who had previously been primed with either DNA or Ad5 alone, the advantages of the heterologous prime boost strategy were evident, with an approximately 7 fold increase in immune responses following Ad5 boosting after DNA priming. This effect was evident in both the T-cell and B-cell compartments [22]. In the HIVIS 03 trial which recruited healthy volunteers in Tanzania, 58% of individuals receiving three injections with multiclade DNA made a positive  $\gamma$ -IFN T-cell Elispot response and this increased to ~100% after boosting twice with MVA. Interestingly, due to problems with product availability, up to 3 years elapsed between the two MVA-CMDR immunisations in this trial. There have been concerns about the dampening effects of vector-specific responses on vaccine immunogenicity and the striking T-cell and B-cell responses seen in this trial may have been due to this (impractically) drawn out schedule.

Apart from intrinsic flexibility and relatively modest manufacturing costs, the rationale for using DNA as a component of HIV vaccines stems also from a desire to induce cytotoxic T cells-responses which depend largely upon the expression of endogenous proteins. Unfortunately, the potency of DNA vaccines first described in animal models has not been realised in the clinic, and this had led to a focus on the development of methods specifically focussed on increasing the efficiency of DNA uptake by cells. Electroporation and the use of needle free devices such as the Biojector have both been shown to increase the immunogenicity of DNA although, to date, electroporation has only been shown to be effective in one clinical trial and the choice of device used is probably key to success [23]. We believe that the cumulative dose of DNA used in priming is crucial in determining the breadth and magnitude of the T-cell response (in this case 12mg given over 8 weeks). The uptake of DNA after IM administration is known to be highly inefficient (~5%) and this may be one of the explanations of the relatively poor performance of DNA vaccines in the clinic. We propose that Electroporation and the Biojector device are included in the proposed trial with the explicit aim of improving the efficiency of uptake of DNA by target cells.

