## 4.2 Participant exclusion criteria

The following are the criteria for exclusion from the study:

1. At risk of HIV infection as mentioned above in the inclusion criteria
2. Active tuberculosis or other systemic infectious process elicited by review of systems, physical examination and laboratory detection (for example detection of Hepatitis B surface antigen or active syphilis)
3. A history of immunodeficiency, ongoing medical and/or psychiatric condition and/or chronic illness requiring continuous or frequent medical intervention
4. Autoimmune disease by history and physical examination
5. Hives or recurrent hives and severe eczema
6. Substance abuse problems (including traditional medicine) during the past 12 months that in the opinion of the investigator would preclude participation
7. History of grand-mal epilepsy, or currently taking anti-epileptics
8. Received blood or blood products or immunoglobulins in the past 3 months.
9. Receiving immunosuppressive therapy such as systemic corticosteroids or cancer chemotherapy
10. Use of experimental therapeutic agents within 30 days of study entry
11. Reception of any live, attenuated vaccine within 60 days of study entry. Medically indicated subunit or killed vaccines (e.g., Hepatitis A or Hepatitis B) are not exclusionary but should be given at least 2 weeks before or after HIV immunisation to avoid potential confusion of adverse reactions.
12. History of cardiac disease including:
  - Previous myocardial infarction (heart attack)
  - angina pectoris; congestive heart failure
  - valvular heart disease
  - cardiomyopathy
  - myo/pericarditis
  - stroke or transient ischemic attack
  - chest pain or shortness of breath at rest or with activity (such as walking up stairs)
  - arrhythmia/episodic palpitations (not excluded: sinus arrhythmia)
  - pacemaker or
  - other heart conditions under the care of a doctor

13. Abnormality in ECG that could indicate risk or make interpretation of vaccine effects difficult according to the study operating procedures. ECG with clinically significant findings, or features that would interfere with the assessment of myo/pericarditis, including any of the following:
  - conduction disturbance (complete left or complete right bundle branch block or nonspecific intraventricular conduction disturbance with QRS >120 ms, an AV block grade II or III, or QTc prolongation [ $> 440\text{ms}$ ])
  - significant repolarisation (ST segment or T wave) abnormality

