### 5.2 Randomisation

There will be two randomization steps. During the first step prior to any vaccination, participants will be randomized according to different DNA immunizations (Groups 1, 2 or 3) and according to vaccine or placebo (A or B). During the second step prior to MVA, vaccination participants will be randomized according MVA (Group A1) or MVA plus gp140/GLA (Group A2) boosting maintaining the placebo affiliation (Groups B1 or B2). Randomisation lists will be drawn up under the supervision of [name]. These will be stratified by centre and gender to ensure a balance between the three active groups and matched placebos. The assignment for each subject will be placed in an envelope with a unique sequential number. Six sets of plain envelopes will be prepared, two for each centre (for males and females) and couriered to the Study Pharmacist for that centre who will take the prepared envelopes and put them in a box that is kept under lock.

The pharmacist will randomise participants accepted into the study, after receiving a copy of the participant's signed informed consent from nurse/doctor, by selecting the next consecutive envelope containing the vaccine or placebo assignment in accordance with the generated randomization list. The Pharmacist will make a record of the assignment and study number in a register held under lock. In the case a subject has to be replaced this is noted in the register; their assignment should not be given to the next volunteer to be randomized. The next volunteer should be allocated the next assignment. The Pharmacist will then inform the Study Nurse/Medical Officer at the clinic of the randomization group, I – III of the participant, but will not inform on whether this is vaccine or placebo. The Study Nurse/Medical Officer will record the group assignment in the study record of the participant's file. Procedures for the second randomisation will be similar. In addition to centre and gender, allocation will be stratified on the outcome of the first randomisation.

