## 7.2 Assessments at screening

### 7.2.1 Demographics, medical history and examination

Demographic information such as age, ethnic origin, smoking, alcohol and illicit drug history will be collected at screening and entered onto the screening CRF.

A past and current medical history will be collected at screening during a face to face structured interview using a case report form, including details of any previous reaction to vaccination, allergies, history of epileptic fit, history of vaccinia (presence of vaccinia scar), reproductive and respiratory symptoms and contraceptive practices (current method and the length of time using the method).

A complete physical examination will be performed. The general examination will include weight (kg), height (cm), temperature, blood pressure, respiratory rate, inspection of the skin to exclude severe eczema and respiratory, cardio-vascular (including ECG, see **section 7.5.3**), abdominal, and neurological examination. An assessment of cervical and axillary lymph nodes will also be undertaken at every visit.

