## 7.3 Other laboratory assessments

### 7.3.1 Antibodies against Vaccinia

Serum samples will be stored at MUHAS, Department of Microbiology/Immunology, MMRC and INS for later testing.

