### Statistical assumptions

Alpha will be reduced to 2.5% ( $p=0.025$ ) to adjust for multiple comparisons of the first randomisation, and will be 5% for the second randomised comparison. The following tables illustrate the power to detect a difference in a continuous variable or proportion with 60 or 90 subjects per group, using magnitude of response, and frequency of responders respectively.

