Prior to the main analysis, the Statistical Analysis Plan will be finalised describing the methods for comparing the groups in detail. The decision to compare the proportion of responders, or the magnitude of response, and the definition for these parameters will be informed by the full analysis of TaMoVac 01 and the results of other relevant clinical trials, with the aim of defining a 'clinically meaningful result'. Proportions will be presented with a confidence interval and groups compared using Fisher's exact test. Response magnitude will be compared between groups using rank tests.

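### The tests named in section 9.5.2 use neither the randomisation strata nor the vaccinia scar recorded at screening, so available precision is left unused

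*Protocol*

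**What the plan says.** **Analysis.** Section 9.5.2 compares proportions by Fisher's exact test. On magnitude it says: "Response magnitude will be compared between groups using rank tests". No stratification factor or covariate is named. The same paragraph leaves the detailed methods, and the choice between proportion and magnitude, to the SAP.

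**Randomisation.** Section 5.2 says of the lists: "These will be stratified by centre and gender to ensure a balance between the three active groups". The second randomisation adds the outcome of the first as a further factor.

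**Vaccinia history.** Section 7.2.1 lists, within the medical history taken at screening, "history of vaccinia (presence of vaccinia scar". Under the heading on vaccinia antibodies, section 7.3.1 says: "Serum samples will be stored at MUHAS, Department of Microbiology/Immunology, MMRC and INS for later testing". Appendix 2 includes vaccinia antibody in the antibody draws at visits 2 and 3. Earlier vaccinia exposure is not an exclusion; section 4.2 item 11 bars only "Reception of any live, attenuated vaccine within 60 days of study entry". The age range is 18 to 40 years (section 4.1).

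**Vector immunity.** Every active participant receives MVA at weeks 24 and 40 (section 6.2). The primary ELISpot result is read 2 weeks after the final vaccination (section 9.2.1.1). Appendix 9 (I)(v) records: "There have been concerns about the dampening effects of vector-specific responses on vaccine immunogenicity".

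**The concern.** A factor used to stratify the randomisation is normally carried into the analysis. If it predicts the outcome, blocking within its levels makes the arms more alike, but an unstratified test still charges that variation to error and forgoes the gain.

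Centre is a plausible predictor here. The ELISpot uses fresh cells (section 7.4.1), and sections 3.1.1 to 3.1.3 describe ELISpot work at each of the three site laboratories, so differences between centres may include differences between laboratories. Prime group is expected to matter for the boost comparison, because the trial's first hypothesis is that the priming method changes the response (section 2.3.1).

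Vaccinia scar is a weaker candidate. It is a baseline marker of possible earlier exposure to the vector family, it is recorded for everyone, and it is neither stratified on nor used in the comparison.

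At stake is sensitivity to smaller effects. Section 9.3 itself concedes that power is insufficient for smaller differences that could still matter. Section 9.2.1.1 restricts magnitude to positive samples, so the numbers analysed fall below 60 or 90 per group if anyone does not respond.

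**Working it through.** **Inputs from the protocol (section 9.3).** n = 60 per group for the first randomisation ("Alpha will be reduced to 2.5" per cent) and n = 90 for the second ("will be 5% for the second randomised comparison"). SD = 0.5 on log10 SFC, stated without any covariate and so read as a total SD. The target effect is a doubling, log10(2) = 0.301.

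**Step 1: reproduce the plan's figures.** Two-sided normal approximation:

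power = Φ( δ / (SD·√(2/n)) − z(1−α/2) )

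- n = 60, doubling, α = 0.025: 0.301 / (0.5·√(2/60)) = 3.298; 3.298 − 2.241 = 1.056; power 85.5% (stated 85%).
- n = 90, 50% increase (log10 1.5 = 0.176), α = 0.05: 0.176 / (0.5·√(2/90)) = 2.362; 2.362 − 1.960 = 0.402; power 65.6% (stated 66%).

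The other four cells of the magnitude table also agree: 66.3% and 37.7% at n = 60 (stated 66 and 38), and 98.1% and 90.3% at n = 90 (stated 98 and 90).

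**Step 2: effect of adjustment.** If the covariates explain a share R² of the total variance, the residual SD is 0.5·√(1−R²). The protocol gives no R², so the range below is an assumption.

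| R² (assumed) | Residual SD | Doubling, n = 60 | 50% increase, n = 90 |
|---|---|---|---|
| 0 | 0.500 | 85.5% | 65.6% |
| 0.02 | 0.495 | 86.2% | 66.5% |
| 0.05 | 0.487 | 87.3% | 67.9% |
| 0.10 | 0.474 | 89.2% | 70.2% |
| 0.20 | 0.447 | 92.6% | 75.2% |

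**Step 3: what scar alone might contribute.** For scar prevalence q and fold reduction g, both assumed, R² = q(1−q)·(log10 g)²/0.25.

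- q = 10%, g = 1.5: R² = 0.011, power for a doubling at n = 60 is 85.9%.
- q = 20%, g = 2: R² = 0.058, power 87.6%.
- q = 50%, g = 2: R² = 0.091, power 88.8%.
- q = 50%, g = 3: R² = 0.228, power 93.5%.

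In the scenarios computed (q from 10% to 50%), a reduction of 1.5-fold or less gives a gain of roughly 1 point at most.

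**Step 4: check with a rank test.** Steps 1 to 3 use means, while the plan names ranks. Simulating 6,000 trials with n = 60, a doubling, q = 30% and a scar effect of 0.3 log10 gives about 83% power for the Mann-Whitney test and 86% for rank ANCOVA on arm and scar. Type I error is near 2.5% for both.

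**Step 5: chance imbalance in scar.** At q = 30%, the 95% limit for the difference in prevalence between two groups of 60 is 1.96·√(2·0.3·0.7/60) = 0.164, or 16 points. With a scar effect of 0.3 log10, that moves the ratio of geometric means by a factor of 10^(0.164·0.3) = 1.12. Centre, gender and prime group are already held close to balance by the stratification; for them the loss is precision only.

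**The case against.** **Appendix 9 does not say what a reader might infer.** It is tempting to read it as stating that pre-existing vaccinia immunity lowers the response to MVA. The remark follows a sentence about a gap of up to 3 years between the two MVA doses in an earlier Tanzanian trial, and it ends by suggesting that the strong responses there may have come from that long schedule. It is a reported concern about spacing. No part of the protocol links scar or baseline vaccinia antibody to response, and Appendix 9 (II)(i) reports 92% and 100% responders after one MVA boost in two earlier trials. This stands: scar is a suspected factor, not a known one.

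**The stated power is not eroded.** A reader might also infer that vaccinia history eats into the claimed 85%. If 0.5 is a total SD, as it reads, that variation is already inside it, and adjustment can only add power. This also stands.

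**The unadjusted tests are valid.** Randomisation protects against bias and type I error, and chance imbalance is covered by the test's error rate. This stands as well; adjustment only offers a correction for imbalance in the trial actually run.

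**The SAP may settle it.** Section 9.5.2 defers detail to a document not shown, and its plural reference to rank tests could include a stratified one. This answers the point only in part. Section 9.5.2 itself names the tests, Fisher's exact test as named is unstratified, and an adjusted primary analysis in the SAP would sit awkwardly with that text.

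**Stratifying proportions may gain little.** If responder rates approach 100%, many strata carry no information. This is fair; the gain is mainly for magnitude.

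**Conclusion.** The point holds as an efficiency improvement, not as an error. The tests named in section 9.5.2 use neither the factors the trial randomises by nor a baseline marker it already collects. The planned power figures reproduce and are not reduced, and the comparisons are neither biased nor invalid.

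The size of the loss cannot be fixed from the protocol. It rests on R², for which no value is given: about 1 to 4 points of power for a doubling at 60 per group if R² is 0.02 to 0.10, about 7 points at 0.20, and none if the factors are unrelated to response. The case is firmest for centre, gender and prime group, because the design already stratifies on them. It is weaker for vaccinia scar, where it rests on an inference from the vector used and not on any effect the protocol reports.

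**What to change.** In section 9.5.2:

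1. Compare magnitude (ELISpot SFC and antibody titre) by a stratified rank test, rank ANCOVA or linear regression on log10 values, choosing one in advance. Include arm and the randomisation factors: centre and gender for the first comparison, plus prime group for the second.
2. Add vaccinia scar (yes/no, from screening) as the one prespecified baseline covariate. Do not provide for replacing it with vaccinia antibody if that is assayed in time; the primary covariate should be fixed beforehand.
3. Compare responder proportions with an exact stratified (Mantel-Haenszel) test by the randomisation factors.
4. Keep the unadjusted Fisher and rank tests as sensitivity analyses.

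The cost is one paragraph and no new data. If the factors prove unrelated to response, a few degrees of freedom are lost. The boost comparison has 3 × 2 × 3 = 18 strata, on average 180/18 = 10 active participants each, and some will be smaller. The text should therefore say how sparse strata are handled, for example by entering the factors as main effects in the magnitude model.
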